## Abstract

**Background:**

Dental caries is a common disease and affects many adults worldwide. Inlay or onlay restoration is widely used to treat the resulting tooth substance loss. Two esthetic materials can be used to manufacture an inlay/onlay restoration of the tooth: ceramic or composite. Here, we present the protocol of a multicenter randomized controlled trial (RCT) comparing the clinical efficacy of both materials for tooth restoration. Other objectives are analysis of overall quality, wear, restoration survival and prognosis.

**Methods:**

The CEramic and COmposite Inlays Assessment (CECOIA) trial is an open-label, parallel-group, multicenter RCT involving two hospitals and five private practices. In all, 400 patients will be included. Inclusion criteria are adults who need an inlay/onlay restoration for one tooth (that can be isolated with use of a dental dam and has at least one intact cusp), can tolerate restorative procedures and do not have severe bruxism, periodontal or carious disease or poor oral hygiene. The decayed tissue will be evicted, the cavity will be prepared for receiving an inlay/onlay and the patient will be randomized by use of a centralized web-based interface to receive: 1) a ceramic or 2) composite inlay or onlay. Treatment allocation will be balanced (1:1). The inlay/onlay will be adhesively luted. Follow-up will be for 2 years and may be extended; two independent examiners will perform the evaluations. The primary outcome measure will be the score obtained with use of the consensus instrument of the Fédération Dentaire Internationale (FDI) World Dental Federation. Secondary outcomes include this instrument’s items, inlay/onlay wear, overall quality and survival of the inlay/onlay. Data will be analyzed by a statistician blinded to treatments and an adjusted ordinal logistic regression model will be used to compare the efficacy of both materials.

**Discussion:**

For clinicians, the CECOIA trial results may help with evidence-based recommendations concerning the choice of materials for inlay/onlay restoration. For patients, the results may lead to improvement in long-term restoration. For researchers, the results may provide ideas for further research concerning inlay/onlay materials and prognosis.

This trial is funded by a grant from the French Ministry of Health.

**Trial registration:**

ClinicalTrials.gov Identifier:
NCT01724827

## Background

The World Health Organization (WHO) estimates the prevalence of dental caries is over 90% among adults worldwide
[1,2]. When the loss of tooth substance due to decay is minor, the dentist fills the tooth cavity. With substantial tooth substance loss, the dentist often treats the tooth with a crown, which presents the problem of further destroying the tooth. Large amalgam or build-up amalgam restorations are also used in such cases in many countries; however, amalgam is being abandoned for environmental reasons, especially in Europe
[3]. An intermediate technique consists of manufacturing an inlay or onlay for the tooth and this type of restoration has become common because it is a minimally invasive solution (further information on inlays and onlays is available at http://cecoia.fr)
[4]. Inlays and onlays can be made of metal alloy, ceramic or composite materials; however, patients tend to refuse metallic restorations for esthetic and financial reasons
[5], and thus dentists generally have to choose between composite and ceramic materials.

The chemical composition differs between ceramic and composite inlays and onlays, and explains most of their clinical properties. Ceramic inlays and onlays (ceramics) are mainly composed of glass, with some crystals added to increase strength
[6,7]. Composite inlays and onlays (composites) are made of a resinous matrix and fillers of different types
[8]. Like glass, ceramics are thus brittle
[9] and more prone to fracture than composites
[10,11]. However, ceramics are harder than composites: they are thus more wear-resistant but can induce more wear than usual with the opposing tooth’s surface
[12]. Furthermore, adhesive cement interfaces are made of composite material, therefore the wear of the interface and restoration material should be closer for composites, with less marginal gaps
[13,14]. Another disadvantage of composites is their resinous matrix. An incompletely polymerized matrix can result in monomers than are released into the mouth, which presents some toxicity, whereas ceramics are extremely biocompatible
[15-19]. A disadvantage of ceramics is that manufacturing is time-consuming; composites are easier to polish and perhaps less costly.

Some factors may influence the clinical performance of ceramic and composite inlays and onlays differently. Ceramics are resistant to compressive forces but susceptible to shear stresses. Increased compressive forces can be expected with onlays, thus the inlay or onlay factor may influence the performance of the materials differently
[10,11]. Bicuspids usually offer more favourable conditions for inlays and onlays than molars: cavities are usually smaller, the effect of masticatory forces and stresses at the adhesive interface are less intense, and access for dental treatment is easier
[20]. Tooth type (bicuspid or molar) may thus influence the performance of composite and ceramic inlays and onlays
[21]. Tooth vitality may also differently influence the clinical performance of both materials; some *in vitro* studies and simulations have suggested that composites could perform better than ceramics for non-vital teeth
[22,23]. Finally, the operator (dentist) who performs the restoration is a key variable
[20,24]; practitioners equipped with the computer-assisted design/computer-assisted manufacturing (CAD/CAM) system (CEREC, Sirona Dental Systems, Long Island City, NY, USA) used in this trial manufacture mostly ceramic inlays and onlays, and may require a slight learning curve to manufacture composite inlays or onlays.

A systematic search of the literature conducted for this report identified only two randomized clinical studies that have compared ceramic and composite inlays and onlays (see Research in context section)
[25-27]. These studies were small in size (43 and 37 patients) and presented some risk of bias. The results from both trials suggested no clear evidence of a difference between ceramic and composite inlays or onlays. Since then, materials have improved, composites (especially as CAD/CAM blocks) have become much safer and consensus outcomes for evaluating dental restorations have been developed
[28].

### Research in context

#### Systematic search of the literature

Following the Cochrane methodology, we searched MED-LINE and Embase for reports of prospective randomized controlled studies comparing at least one composite and one ceramic material for inlay or onlay manufacturing, with a minimum follow-up of 6 months, and without any date or language restriction up to 11 October 2012.

#### Studies identified through the systematic search

*In vitro*: 91 studies

Only one ceramic or one composite (no control or luting agent/base material randomized): 20 studies (27 reports)

Ceramic versus ceramic: three studies

Composite versus composite: two studies

Ceramic versus composite (non-randomized or retrospective study): five studies (eight reports)

Ceramic versus composite (prospective randomized study): two studies (four reports)

#### Interpretation

Only two randomized studies were identified, which compared ceramic and composite materials for inlay or onlay manufacturing. In 2005, a study compared 80 VITA Mark II (ceramic; Vita Zahnfabrik, Bad Säckingen, Germany) and Paradigm (composite; 3M Espe, St Paul, MN, USA) CAD/CAM inlays in 43 adults after 3 years with use of the US Public Health Service (USPHS) modified criteria
[29]. The composite inlays performed better for only two items: color match and restoration fracture
[25]. In 2006, a study compared 58 CEREC, Vita Dur N (two ceramics; Vita Zahnfabrik), Brilliant DI (Coltene/Whaledent AG, Altstätten, Switzerland) and Estilux (two composites; Heraeus Kulzer GmbH, Hanau, Germany) inlays in 37 patients after 10 years with use of the California Dental Association criteria
[30]: survival was similar for all inlays when repairs were not considered failures (75 to 80%) and was better for CEREC ceramic inlays than other inlays when repairs were considered failures (80% versus 51 to 67%)
[26]. Data on the material to use for manufacturing inlays or onlays are thus controversial and a RCT is needed.

The main objective of the CEramic and COmposite Inlays Assessment (CECOIA) randomized controlled trial (RCT) is to compare the clinical efficacy of composite and ceramic inlays or onlays for treating moderate substance loss of posterior teeth in adults according to recent consensus outcomes. Secondary objectives include the overall quality, wear and survival of inlays and onlays made of both materials, and prognostic factors of restoration failure, including patient-related items.

## Methods

This trial is a multicenter, randomized, open-label superiority trial with two balanced parallel arms. The trial received approval from the French ethics committee for the protection of persons (Comité de Protection des Personnes (CPP), Ile de France XI, trial number 12029) in May 2012.

### Participants and setting

#### Eligibility criteria for patients

Patients are eligible to participate in the trial if they are adults aged 18 to 70 years, can tolerate restorative procedures and have a posterior moderate-sized dental caries or aged restoration necessitating an inlay or onlay. Exclusion criteria are allergy to one of the materials used, bruxism, severe or acute periodontal or carious disease (greater than or equal to four primary or secondary restorations due to caries in the preceding year) and poor oral hygiene; the tooth to be treated should not need endodontic treatment or retreatment, show mobility >1 mm or a periodontal socket >3 mm or support a removable partial denture.

Patients with a tooth showing a subgingival margin after cavity preparation, that cannot be isolated with use of a rubber dam, or that has cusps that all need to be covered by the restoration are not eligible.

Only one tooth per patient is eligible. If a patient needs more than one inlay/onlay restoration, the tooth with expected cervical limits that are the most coronal, is the eligible tooth. Other required inlays or onlays will be manufactured by the dentist with the usual material (leucite-reinforced glass-ceramic). In case of pulpal exposure, the operator will decide whether a direct pulp capping (with calcium hydroxide) or an endodontic treatment is necessary, randomize the patient after this treatment has been conducted and fill the corresponding fields in the adverse events section of the case report form (CRF).

#### Eligibility criteria for operators (dentists)

Operators will be eligible for inclusion if they have at least 3 years of clinical experience and at least 1 year of experience with chairside CAD/CAM, agree with the intervention protocol, and have no preference for either composite or ceramic to manufacture inlays and onlays.

#### Eligibility criteria for evaluators

Evaluators of restorations during follow-up will be two dentists different from the operators.

#### Setting

Patients will be included and treated in seven centers in France: the dental care departments of two hospitals (Hôpital Charles Foix, Ivry-sur-Seine and Hotel-Dieu Saint-Jacques, Toulouse) and five private practices (four in Paris and one in Lyon). Follow-up data will be collected in these seven centers. Any patient with the eligible criteria visiting one of the included centers will be asked to participate in the study. The consent form can be consulted at http://cecoia.fr: extra section.

### Interventions

Patients will be allocated to receive a leucite-reinforced glass-ceramic or a composite CAD/CAM inlay or onlay.

Among the ceramics currently used, we chose a pressed glass-ceramic because fired feldspathic ceramics have shown higher fracture rates
[31], and we chose leucite-reinforced glass-ceramic (IPS Empress CAD, Ivoclar Vivadent, Schaan, Liechtenstein) over lithium disilicate-reinforced glass-ceramic because the latter has been frequently evaluated clinically. Among available composites, we chose a recently developed material (Lava Ultimate, 3 M ESPE, St Paul, MN, USA), which we considered promising after laboratory testing.

Although the purpose was not to study CAD/CAM but to compare composite and ceramic as inlay or onlay materials, we decided to use CAD/CAM for the inlays or onlays in this trial to standardize the manufacturing (as compared with the necessary variability with a dental technician). This technology also simplifies the protocol and conduct of the trial, since some CAD/CAM systems allow for manufacturing inlays or onlays chairside during a single appointment.

For cavity preparation, the operator will choose the color for both evaluated materials (A1/A2/A3). With the patient under local anesthetic, if needed, the cavity will be prepared (for dental caries or former restoration eviction) using a burs sequence (Komet, Rock Hill, SC, USA) specifically designed for the CECOIA trial. Adjacent teeth will be protected (FenderWedge, Directa, Upplands Väsby, Sweden)
[32,33]. The following thicknesses will be respected: 2 mm wide and 1.5 mm deep for isthmuses, and 1.2 mm wide for approximal boxes, the approximal overhang not exceeding the box width. Cusps will be covered if the width of the isthmus is greater than half of the intercusp buccolingual distance, the wall is ≤2 mm thick before preparation, the wall is ≤1 mm thick after preparation, the width of the isthmus is close to half the intercusp buccolingual distance and one or more cracks are observed or the preparation is mesio-occlusal-distal or with horizontal forces
[34-36]. A base can be applied (dental dam; OptiBond XTR and Premise Flowable, Kerr, Orange, CA, USA).

#### Computer-assisted design/computer-assisted manufacturing (CAD/CAM)

After powder spraying (CEREC Optispray, Sirona Dental Systems), the operator will scan the preparation with use of a digital camera and design the restoration by use of CEREC software (Sirona Dental Systems). If eligibility criteria are still satisfied, the operator will then randomize the tooth to a treatment (randomization procedure described below), insert the corresponding block inside the milling machine and press the button for the restoration to be milled. The operator will then check the approximal contacts of the resulting restoration, correct them if need be, remove the machining lug and weigh the restoration.

#### Surface treatment and polishing of ceramic inlays or onlays

The operator can glaze (IPS Object Fix Putty, glazing paste and stains, Ivoclar Vivadent) or polish the inlay or onlay using the polishers provided in the sequence and diamond paste (OptraFine, Ivoclar Vivadent). The intaglio surface will then be treated with hydrofluoric acid (Porcelain Etchant gel, Bisico, Schaumburg, IL, USA) for 60 seconds, rinsed, dried, silanated (Monobond Plus, Ivoclar Vivadent) and left to dry for at least 3 minutes before sealing.

#### Surface treatment and polishing of composite inlays or onlays

The operator will polish the inlay or onlay using the polishers provided in the sequence, and may modify the color (Kolor Plus, Kerr) of pits and fissures. The intaglio surface will be sandblasted with 50 μm alumina, rinsed, dried, silanated (Monobond Plus) and left to dry for at least 3 minutes before sealing.

#### Inlay or onlay adhesive luting and finishing

A dental dam (DermaDam medium, Bisico) will be used. The tooth surface will be cleaned by air abrasion (RONDOflex, KaVo, Biberach, Germany). Enamel will be etched with orthophosphoric acid (37.5%) for 15 seconds, rinsed thoroughly and dried gently
[37]. Adhesive (Optibond XTR) will be applied by gently brushing the tooth surface for 15 seconds, followed by a 3-second air spray and light polymerization of the adhesive for 20 seconds. The inlay will be handled with use of a stick (Stik-N-Place, Directa); adhesive cement (NX3 yellow, Kerr) will be applied generously on the intaglio surface of the restoration. The inlay or onlay will be positioned and maintained. It may be light polymerized for 1 or 2 seconds. Excess cement will be carefully removed by use of dental floss and a curette. Glycerine gel will be applied on the limits of the restoration, followed by light polymerization of the cement for 40 seconds per face. The occlusion will then be adjusted, and the corrected surfaces and cement interface will be polished.

### Outcomes

#### Primary outcome

The primary outcome, clinical efficacy of materials, will be measured by use of the Fédération Dentaire Internationale (FDI) World Dental Federation instrument for assessing dental restorations, described in 2007
[28] and updated in 2010
[38]. This instrument contains three dimensions (18 items): biological (six items), functional (seven items) and esthetic (five items). Each item is assessed by clinical examination on a 5-point Likert scale (1 corresponding to a perfect restoration and 5 corresponding to a restoration that needs to be replaced), and collected in the CRF. All items but one are assessed by the dentist; the remaining item is patient-reported satisfaction. The primary outcome is the worst score for all items (ranging from 1 to 5) at 2-year follow-up (the best material will be the one with the lowest score).

Operators and evaluators, who will assign scores, will be trained in the FDI criteria by means of the e-calib web-based  software (http://zep01793.dent.med.uni-muenchen.de/moodle/) and group training sessions. They will use the evaluation kit specifically designed for evaluating the FDI criteria (EX-KIT 150/250, Deppeler, Rolle, Switzerland).

#### Secondary outcomes

Secondary outcomes will include each item of the FDI instrument, patient-relevant outcomes, quantified wear analysis (through silicone impressions) and overall quality of the restoration (as assessed by dentists). Survival may be evaluated if the follow-up is extended.

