### Blinding/masking

Operators cannot be blinded to the randomization because the intervention differs between both arms (in particular, surface treatments of the upper and intaglio surfaces of the restoration). Moreover, a dentist can easily recognize each material, so neither operators nor evaluators can be blinded. Patients are not blinded, firstly because a few patients had been asked if they would prefer one material to the other and most did not have any preference; secondly because it would complicate the clinical session because the block is inscripted with the name of the material and the intervention differs between both arms; and thirdly because another dentist could tell them if their restoration is made of composite or ceramic.

Therefore, the trial will be open-label. Randomization was thus planned as late as possible to insure that the tooth cavity would be prepared in the same way for both groups and to limit bias due to the absence of blinding. Interventions were standardized as much as possible (in particular, similar adhesive luting procedure) to enhance similarity. The statistician will be blinded to the treatment arms during data analysis.

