#### Secondary outcomes analysis

The same analyses will be used to compare both treatments by each of the three dimensions (with an α risk of 1.7% for each dimension). Secondary analyses will also involve FDI items, quantified analysis of wear (by silicone impressions) and analysis of the overall quality of the restoration (assessed by dentists).

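### The reasons given for open-label assessment do not reach wear measured on silicone impressions, and no masking is stated for that reading

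*Protocol article*

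**What the plan says.** Wear is a named objective of the trial. The article states that "Secondary objectives include the overall quality, wear and survival of inlays and onlays made of both materials" (Research in context, Interpretation). The Secondary outcomes section gives the medium: "quantified wear analysis (through silicone impressions"). The Secondary outcomes analysis section repeats it: "quantified analysis of wear (by silicone impressions) and analysis of the overall quality of the restoration (assessed by dentists"). Table 1 schedules impressions at 1 week, 1 year and 2 years.

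The Blinding/masking section takes the roles one at a time:

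- Operators: "Operators cannot be blinded to the randomization because the intervention differs between both arms".
- Evaluators: "a dentist can easily recognize each material, so neither operators nor evaluators can be blinded".
- Patients: they are not blinded either, for reasons that include the name of the material on the block and the chance that another dentist tells them.
- Conclusion: "Therefore, the trial will be open-label". No outcome is excepted.
- Statistician: "The statistician will be blinded to the treatment arms during data analysis". No other role is said to be blinded.

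The Background gives a direction for wear: "ceramics are harder than composites: they are thus more wear-resistant". It adds that ceramic may cause more wear of the opposing tooth.

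**The concern.** The open-label conclusion is drawn for the trial as a whole, but the argument for it rests on contact with the restoration: doing the procedure, or seeing the material in the mouth. Wear is quantified from an impression, which reproduces surface shape and carries neither the color nor the substance of the restoration. The argument therefore does not cover this outcome, while the conclusion does.

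What is at stake is detection bias in a named secondary objective. The article itself states which material should wear less. If the person measuring wear knew the arm, and the method left room for judgement, readings could drift toward that expectation. The FDI items that a dentist scores, and the dentist-rated overall quality, depend on looking at the restoration and are hard to mask. Wear is the outcome for which masking the assessor looks feasible. The section lists steps to limit bias from the lack of blinding (late randomization, standardized procedures, a blinded statistician) but not this one.

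**Working it through.** **Setting the sections side by side.** The question is whether each stated reason for not blinding applies to someone who measures an impression.

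| Reason in Blinding/masking | What it depends on | Applies to reading an impression? |
|---|---|---|
| The operator's procedure differs by arm | Performing the intervention | No, unless the operator is also the reader, which is not stated |
| A dentist recognizes the material | Seeing the restoration | Not directly: the impression shows shape only. Surface detail might still give a hint |
| The patient may see the block or be told | Being the patient | No |

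None of the three supports leaving the reading of impressions unmasked.

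**What the article leaves open.** Every mention of wear and impressions (Abstract, Interpretation, Secondary outcomes, Table 1, Secondary outcomes analysis) is silent on who measures, by what method, and how the impressions are labelled. The two evaluators examine restorations at 1 and 2 years and assign FDI scores. The article does not assign them the impression reading.

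**Size.** The plan has no figure of its own to reproduce: it gives no SD, expected difference or sample size for wear. The following only illustrates how sensitive a trial of this size is to a reading shift.

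- Number per arm: 358 / 2 = 179. The 358 comes from the Sample size section. It was derived for the FDI score after inflation for center and operator correlation, and is borrowed here as a plausible evaluable number.
- Standard error of a standardized mean difference: √(2/179) = 0.106 SD. This treats patients as independent.
- Assumed systematic shift between arms, with no true difference: 0, 0.1 or 0.2 SD. These values are assumptions without a source in the documents.
- False-positive rate at two-sided 5%: P(|Z| > 1.96), where Z has mean shift/SE and variance 1.

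| Assumed shift | Shift / SE | False-positive rate |
|---|---|---|
| 0 | 0 | 5% |
| 0.1 SD | 0.1 / 0.106 ≈ 0.95 | 0.157, about 16% |
| 0.2 SD | 0.2 / 0.106 ≈ 1.89 | 0.473, about 47% |

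Any continuous outcome would give the same percentages under the same assumed shift. They show that small shifts would matter at this sample size, not that such shifts will occur.

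**The case against.** A reader might infer that wear will be read open-label, because the trial is called open-label and only the statistician is said to be blinded. The documents do not support that. The Blinding/masking section never mentions a wear reader, and its description of the trial as a whole does not rule out a masked laboratory reading. Silence about a role is not a statement that the role is unblinded.

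The further objections are fair:

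- The article condenses a full protocol that it says is available on the trial website. Reader identity, labelling and measuring method for one secondary outcome are the kind of detail an article leaves out.
- The Data collection section says patients are identified by inclusion number, and nothing suggests that this number reveals the arm. A ban on using it is not shown to be needed.
- The outcome is described as quantified. A largely instrumental method would leave less room for judgement.
- Wear is a change over time, so impressions of the same tooth must be linked. Masking the visit may not be compatible with the method.
- The 16% and 47% rest on assumed shifts and on a number of patients calculated for another outcome.

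All of this limits the strength of the point. It does not remove it. The article does not defer blinding to another document: it gives a dedicated section with reasons and countermeasures. Those reasons stop short of the impressions, and the countermeasure that the impressions allow is not among those listed.

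**Conclusion.** The point holds as a gap in the reasoning on blinding and as an opportunity for a cheap improvement. The grounds for open-label assessment do not extend to wear quantified on silicone impressions, no masking is stated for that reading, and the article sets an expectation about its direction.

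It is not established that the reader knows the arm, or that any bias will arise, and the size of any bias cannot be estimated from the documents. The false-positive rates of about 16% and 47% are illustrations that depend on assumed shifts of 0.1 and 0.2 SD, 179 independent patients per arm and no true difference. The conclusion also assumes that an impression does not readily identify the material. The effect is confined to one secondary outcome. The primary FDI score, obtained by clinical examination plus one patient-reported item, is unaffected.

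**What to change.** In the Secondary outcomes and Blinding/masking sections, state that:

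1. impressions, and any casts made from them, are labelled with a code that does not reveal the arm;
2. wear is quantified by a person without access to the allocation, who is masked to visit order as well only where the measuring method allows it;
3. the code is broken after the wear data are locked.

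The impressions are already scheduled, so no visit or procedure is added. Coding can be done at any time before reading, so the change remains possible after recruitment has begun. The cost is the work of relabelling impressions from seven centers at three time points, with someone outside the reading to hold the key. The documents give no basis for pricing that work. Masking may be incomplete if surface detail hints at the material. No sample size, power or significance level changes.
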